## Abstract

**Background:**

Prolonged physical impairments in range of movement, postural stability and walking speed are commonly reported following total hip replacement (THR). It is unclear from the current body of evidence what kind of exercises should be performed to maximize patient function and quality of life.

**Methods/design:**

This will be a single blind multi centre randomized control trial with two arms. Seventy subjects post primary total hip arthroplasty will be randomized into either an experimental group (n=35), or to a control group (n=35). The experimental group will attend a functional exercise class twice weekly for a six week period from week 12 to week 18 post surgery. The functional exercise group will follow a circuit based functional exercise class supervised by a chartered Physiotherapist. The control group will receive usual care. The principal investigator (BM) will perform blinded outcome assessments on all patients using validated measures for pain, stiffness, and function using the Western Ontario and Mc Master Universities Osteoarthritis index (WOMAC). This is the primary outcome measurement tool. Secondary outcome measurements include Quality of life (SF-36), 6 min walk test, Visual Analogue Scale, and the Berg Balance score. The WOMAC score will be collated on day five post surgery and repeated at week twelve and week eighteen. All other measurements will be taken at week 12 and repeated at week eighteen. In addition a blinded radiologist will measure gluteus medius cross sectional area using real time ultrasound for all subjects at week 12 and at week 18 to determine if the functional exercise programme has any effect on muscle size.

**Discussion:**

This randomised controlled trial will add to the body of evidence on the relationship between muscle size, functional ability, balance, quality of life and time post surgery in patients following total hip arthroplasty. The CONSORT guidelines will be followed to throughout. Ethical approval has been gained from the Ethics committee Health Services Executive Dublin North East.

**Trial registration:**

This trial is registered with ClinicalTrials.gov (a service of the United States National Institutes of Health) identifier NCT01683201

## Background

Total hip replacement (THR) is a very common surgical procedure carried out worldwide. Approximately 24,253 THR surgical procedures were performed in Canada in 2008/09 [1] with almost one million hip and knee replacements undertaken in the U.S in the same time-frame. [2] In England and Wales 53,462 hip replacements were undertaken in 2009 including both primary and revision joint procedures [3]. These figures have been projected to grow with the aging population and with the increased prevalence of arthritis in the elderly [4]. Improvements in prosthetic design and higher community expectations for quality of life have made THR more appropriate for both older and younger age groups resulting in an increased population and healthcare demand for surgery [5].

In recent years the shift towards reductions in the length of stay for patients following THR has caused a subsequent shift in rehabilitation services from ’in hospital’ to out patients [6]. Within the outpatient setting however a number of authors have reported functional limitations for patients post surgery. Pain, physical impairment, reduced range of motion and reduced muscle strength persisting for one year have been documented in subjects who had also received early stage physiotherapy [7]. It is currently unclear from the literature which therapeutic exercises performed over what period of time are either effective or necessary to improve muscle strength or ensure optimal return of patient function. Anecdotally therapeutic exercise programmes appear to be largely based on clinical experience and surgeon preference [8]. Some evidence [9] has demonstrated that an eight week exercise programme with an emphasis on strengthening and stability resulted in a statistically significant improvement in all measurements of self perceived function and muscle strength in patients between four and twelve months post THR. It has been suggested in this study that patients should continue their functional strengthening exercise programme for at least one year and that this programme should be further progressed as their function improved.

Another study [10] compared differences in the isometric hip strength of patients five months after THR with older adults without hip surgery and demonstrated lower peak torque in the hip flexors of the hip surgery group. Specific rehabilitation programmes are needed to address these strength deficits at this phase post surgery although few studies to date have evaluated this subject.

The gluteus medius muscle is critical to the provision of abduction force across the hip and the strength of the muscle is specifically relevant to the provision of stability in the hip joint [11]. Post operative function is determined by regaining the optimal strength in this muscle and many rehabilitation programmes include strengthening of gluteus medius. The strength of this muscle provides lateral stability to the trunk and pelvis and is essential during one legged stance and also during the stance phase of gait [12]. However there is a paucity of evidence in the literature examining specific changes in this muscle despite anecdotal evidence that reduced strength in this muscle is responsible for gait impairment and reduced balance [13].

Recognizing the difficulties in measuring rehabilitation of glutei dysfunction it has been suggested that future studies on the glutei muscles should evaluate each muscle in functional activities preferably using multiple parameters for example evaluation of muscle size together with functional assessment [14]. Recently real time ultrasound imaging has been utilized as an accurate and reliable means of measuring muscle parameters in a non invasive manner [15,16]. Ultrasound imaging is a fast and inexpensive tool that produces excellent images of the musculoskeletal system without the need for radiation [17].

The primary aim of this research project is to evaluate the efficacy of a specific functional exercise programme to improve pain stiffness and physical function in patients between 12 and 18 weeks post THR when compared with a group following usual care. In addition this project aims to measure the effect of a functional exercise programme on the secondary outcomes of quality of life, balance, function and muscle size. Muscle size measured by real-time ultrasound was selected as an additional secondary outcome in order to examine specific changes in the gluteus medius muscle.

In preparing this protocol a full systematic review and meta-analysis of previous work has been completed. This review found there was low grade evidence that late stage rehabilitation demonstrated significant improvement in gait speed indicating improved walking ability in patients post total hip arthroplasty and there was limited low grade evidence for improved hip abduction strength in patients following a programme which included low resistance strength training. However the full extent of the impact of late stage rehabilitation in patients post total hip arthroplasty has not yet been established. These issues were considered in designing this randomized controlled trial.

Other preparatory work to prepare this protocol included preliminary clinical patient evaluation in a single elective orthopedic centre. A telephone questionnaire of 120 patients in 2009 at 12 weeks post surgery demonstrated approx 30 % of patients contacted reported persistent limping and gait abnormalities at 12 weeks. These patients were not previously referred to Physiotherapy. A second telephone survey evaluated ten centers nationally which carry out elective hip arthroplasty and demonstrated a wide diversity of rehabilitation offered across the country and a paucity of evidence based practice guidelines for this client group.

The primary aim of this research project is to evaluate the efficacy of a specific functional exercise programme to improve pain, stiffness and physical function in patients between 12 and 18 weeks post total hip replacement when compared with a group following usual care. In addition this project aims to measure the effect of a functional exercise programme on the secondary outcomes of quality of life, balance, function and muscle size. Muscle size measured by Real time ultrasound was selected as an additional secondary outcome measuring specific changes in the gluteus medius muscle. There is a paucity of evidence in the literature examining specific changes in this specific muscle despite anecdotal evidence that reduced strength in this muscle is responsible for gait impairment and reduced balance.

### Primary hypotheses

A six week functional exercise programme from week 12 to week 18 in patients post total hip replacement will be more efficacious in improving pain, stiffness and function than the usual care programme.

### Secondary hypotheses

A six week functional exercise programme from week 12 to week 18 in patients post total hip replacement will be more efficacious in improving balance, gait speed, quality of life and muscle size than the usual care programme.

## Methods/design

### Trial design

This will be an assessor blinded two arm randomized controlled trial of a six week involving twelve functional exercise class interventions. Measurements will be taken at day five, week twelve and week eighteen for all subjects. Assessment of adherence to the treatment programme will be assessed with examination of exercise logs completed by clients at each attendance and signed off by the supervising therapist. The classes will be conducted at three sites, Navan, Cavan and Monaghan. The protocol will conform to CONSORT guidelines for reporting non-pharmalogical interventions and has been registered with clinical trials.gov prior to study commencement.

### Participants

We will recruit participants at pre-assessment for primary total hip replacement at Our Lady’s hospital, Navan which is the elective joint replacement for the Louth/Meath and Cavan/Monaghan areas. To be eligible the following inclusion and exclusion criteria must be met.

### Inclusion criteria

Patients 12 weeks post primary unilateral anterior approach THA for osteoarthritis.

Age 50 years and above.

Able to read and understand instructions in English.

Willing to attend classes twice weekly for 6 weeks

Able to participate in an exercise programme without physical assistance.

Mobilizing independently 15m without crutches and/or stick and passed by the referring Orthopaedic consultant as suitable for inclusion in the study at the routine six week post surgery appointment.

### Exclusion criteria

Medically unstable.

Have central or peripheral nervous system deficits.

Any underlying terminal disease.

Suspicion of infection following joint replacement.

### Procedure

Preliminary screening will be carried out at the pre-assessment clinic by the principal investigator (BM). Following a standard interview process patients will be given a written description of the study and information with regard to the exercise class commitment involved. A screening record will be kept to document criteria eliminating those deemed to be ineligible. All patients will all be assessed using the WOMAC questionnaire on day 5 prior to discharge and they will be randomized to one of two treatment groups. The functional exercise intervention begins at week 12 and all patients will complete the Primary and Secondary outcome assessments at this point. All assessments are repeated for both groups at week 18. Patients allocated to the functional exercise class will attend a six week functional exercise programme twice weekly from week 12 to week 18. The control group will receive the standard usual post surgery care as outlined in the patients’ information booklet given to all patients on admission. This care is given to all patients post surgery by the Physiotherapist working on the ward. This study is one comparing usual treatment with an intervention of functional exercise. All patients randomised to the usual care group will be offered the chance to attend the exercise group at week 18 post evaluation.

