### Randomisation and allocation concealment

Following a standard interview at the pre assessment clinic, Patients will be given a written description of the study and information with regard to the exercise class commitment involved. They will also be given stamped addressed envelopes to post back written consent. Following obtainment of written consent random allocation using sequentially numbered envelopes to both groups will be carried out by a third party [name] (LBC) who is not involved in the study. The number sequence will be generated using a computer generated random number table generated by [name] and communicated directly to LBC. Subjects will be randomly allocated either to a functional exercise class from week 12 post op to week 18 or to a control group receiving usual post operative care. Allocation of patients to the treating therapists will be established by e mail contact from LBC to the Physiotherapist’s responsible for conducting the classes. These therapists have been identified previously. Patients will be asked not to discuss their group allocation and all blinded outcome assessment examinations will take place in Our Lady’s Hospital, Navan.

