#### Statistical analysis

Data analysis will be performed in consultation with [name] in CSTARS. The primary conclusions of this project will be based on analyses conducted under the principal of intention to treat. All randomised patients will be analysed in the groups to which they are originally allocated to regardless of whether they actually received the intended treatment or not. Missing primary outcomes will be assumed to be missing at random and will not be considered in the primary analysis.

Primary analysis of the effect of functional exercise will incorporate continuous variables which are expected to be normally distributed. These will be presented as mean and standard deviations and will be assessed using t tests at different time points i.e. at 12 weeks and again at 18 weeks. If the data is not normally distributed it is planned to use the non parametric Wilcox on signed ranks test.

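### Randomisation is placed before eligibility can be settled, and its time is not fixed, so some randomised patients may later prove ineligible and the week 12 self-reports may be given with the arm known

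*Protocol article*

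**What the plan says.** All references are to the protocol article.

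- **Recruitment** (Participants): "We will recruit participants at pre-assessment for primary total hip replacement", that is, before surgery. The Procedure section calls the screening done there preliminary.
- **Randomisation, first statement** (Procedure): patients are "assessed using the WOMAC questionnaire on day 5 prior to discharge and they will be randomized to one of two treatment groups".
- **Randomisation, second statement** (Randomisation and allocation concealment): consent forms go home with the patient ("They will also be given stamped addressed envelopes to post back written consent"), and then "Following obtainment of written consent random allocation using sequentially numbered envelopes to both groups will be carried out by a third party". No surgical milestone is attached.
- **Eligibility** (Inclusion criteria): "Patients 12 weeks post primary unilateral anterior approach THA for osteoarthritis", walking 15 m without aids, and "passed by the referring Orthopaedic consultant as suitable for inclusion in the study at the routine six week post surgery appointment". The Exclusion criteria add suspected infection after the replacement.
- **Analysis set** (Statistical analysis): "All randomised patients will be analysed in the groups to which they are originally allocated", whether or not the treatment was received. Missing primary outcomes are taken as missing at random and left out.
- **Blinding** (Blinding; Randomisation and allocation concealment): the outcome assessors and the statistician are blind. Patients are asked to keep their allocation to themselves, which presumes that they know it at some stage.
- **Start of treatment** (Procedure): the classes begin at week 12, when all primary and secondary outcomes are assessed.

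**The concern.** Randomisation protects the comparison only from the moment of allocation, and only for the patients allocated. Here six to twelve weeks or more can pass between allocation and the point where a patient can be called eligible. A patient who fails clearance at week 6, or has a suspected infection, has three possible fates:

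1. Removal after randomisation, which contradicts the intention-to-treat rule and could differ by arm, since only one arm faces twice-weekly classes.
2. No week 18 outcome, in which case the patient leaves the primary analysis under the missing-at-random rule.
3. Retention and analysis without the intervention, which pulls the estimated difference towards zero.

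The second issue is the week 12 assessment. WOMAC, SF-36 and the pain VAS are self-reported. If patients have been told their arm by then, the pre-intervention scores are open to expectation effects. Week 12 is the first measurement for SF-36. WOMAC has a day 5 value, as does the VAS according to Table 2.

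**Working it through.** **Order of events.** The stated steps line up as follows.

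| Time | Step | Section |
|---|---|---|
| Pre-assessment | Preliminary screening, consent form given | Procedure; Randomisation |
| After posted consent | Allocation (second statement) | Randomisation |
| Day 5 | WOMAC, allocation (first statement) | Procedure |
| Week 6 | Consultant clearance | Inclusion criteria |
| Week 12 | Time-since-surgery criterion met, assessments, classes start | Inclusion criteria; Procedure |

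Under either statement, allocation comes before the last two rows. No section describes an eligibility check before the envelope is opened.

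**The plan's own sample size.** Inputs from Sample size: difference 10.4, SD 13.6, two-sided 0.05, power 80%.

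- d = 10.4/13.6 = 0.765.
- n per arm = 2(1.96 + 0.842)²/0.765² ≈ 26.8, so 27 per arm and 54 in total; 54/0.9 = 60. The stated figures reproduce (the t-based value is 27.8, or 28 per arm).
- With 70 randomised and 10% attrition, 63 remain and t-based power is 85%.

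**Effect of ineligibility.** The documents give no rate x. I assume 10%, 20% and 30%, with the 10% attrition on top.

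*Lost from analysis.* Patients left = 70 × (1 − x) × 0.9.

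*Kept with no benefit.* All 63 are analysed (31.5 per arm), and the difference becomes 10.4 × (1 − x) with the SD held at 13.6.

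Power ≈ Φ(δ/σ × √(m/2) − 1.96), with m per arm. Example, lost at 10%: m = 28.35, so 0.765 × √14.175 = 2.88, and Φ(0.92) = 82%. The noncentral t gives 81%.

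| Assumed x | Left if lost | Power, t (normal) | Difference if kept | Power, t (normal) |
|---|---|---|---|---|
| 10% | 56.7 | 81% (82%) | 9.4 | 77% (78%) |
| 20% | 50.4 | 76% (78%) | 8.3 | 67% (68%) |
| 30% | 44.1 | 70% (72%) | 7.3 | 55% (57%) |

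To keep 54 evaluable when ineligible patients are lost, the number to randomise is 54/((1 − x) × 0.9) = 67, 75 or 86.

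**The case against.** Several points on the other side are sound.

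- **The timing is loosely worded.** Following consent is only an earliest bound, and the Procedure sentence joins day 5 and randomisation with a plain conjunction. The Abstract speaks of randomising subjects who have already had surgery, which speaks against allocation before the operation. That leaves the time unfixed, but nothing in the text moves it to week 12.
- **Early knowledge of the arm is not stated.** A reader might infer that patients know their arm for up to twelve weeks and that the week 12 baseline is spoiled. No section says when they are told, and the request not to discuss allocation fits disclosure at week 12 as well. Only the possibility stands.
- **The harm through week 12 scores is limited.** The Statistical analysis section plans t tests at each time point. As worded, the week 18 comparison uses neither change from week 12 nor adjustment for it.
- **Non-receipt is already covered.** Patients are analysed as allocated whether treated or not. That rule answers how untreated patients are classed; it does not say whether someone who fails an inclusion criterion stays in the trial and is followed up.
- **Differential exclusion is not shown.** Allocation is e-mailed to the class therapists, and nothing says the clearing consultant sees it. Nothing says the consultant is blind either.
- **The trial has a margin on WOMAC.** With 54 needed and 70 planned, total loss of 16/70, about 23%, is tolerable on the plan's own formula. It would be wrong to say that the 10% allowance alone must absorb eligibility failures.
- **The roughly 30% with limping or gait abnormality in the Background is no eligibility failure rate.** A patient can limp and still walk 15 m unaided, so that figure neither estimates nor bounds x.

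**Conclusion.** The sequence problem is firm: the article gives two loosely worded times for randomisation, and both precede the points at which its own criteria can be met. As written, some randomised patients may later prove ineligible, and the article does not say what happens to them. That is more than a detail left out of a condensed article, because the stated order conflicts with the stated criteria and sits badly with the stated analysis rule.

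The consequences are conditional. The power figures illustrate assumed ineligibility of 10% to 30% with a further 10% attrition; the lower set also assumes full follow-up of the 63 and no benefit at all in ineligible exercise patients. If ineligible patients are lost, about 10% ineligibility leaves WOMAC power at 81%, and the shortfall begins at higher rates. If they are kept without benefit, power is already 77% at 10%. A reader might conclude that the trial is underpowered or that its baseline is biased; the documents support neither as a fact, since they give no ineligibility rate and no date of disclosure. The point still merits correction before recruitment, because exclusions after randomisation cannot be repaired at analysis.

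**What to change.** Keep consent at pre-assessment and the WOMAC at day 5. Open the next sequential envelope only at week 12, after eligibility is confirmed and all week 12 assessments are complete; the third party then e-mails the allocation to the therapist. State this one time in both sections, and define the intention-to-treat set from that point. The target of 70 randomised and the WOMAC calculation need no change.

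The cost is an amendment, shorter notice for booking classes, and more patients consented than randomised. At the assumed rates, and counting eligibility failures only, randomising 70 means consenting 70/(1 − x) = 78, 88 or 100 patients, which should be checked against the January 2014 completion date in Timelines.

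If allocation has to stay early, the smaller repair is to state its exact time, have eligibility judged by someone blind to arm, keep every randomised patient in follow-up and analysis, and allow for ineligibility in the sample size.

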### Ethical considerations

This study obtained ethical approval from the HSE Research Ethics Committee Dublin North East Area in December 2011 for the clinical sites at Our Lady’s Hospital, Navan, Cavan General Hospital and Monaghan General Hospital.

### Blinding

Both outcome assessors will be blind to group allocation and will not be involved in the interventions nor will they attend any of the functional exercise classes. The physiotherapists supervising the functional exercise classes are not blinded. The statistician will be blinded to group allocation prior to completion of the statistical analysis.

